## Abstract

**Background:**

Many self-management programs have been developed so far. Their effectiveness varies. The program ‘Beyond Good Intentions’ (BGI) is based on proactive coping and has proven to be (cost-) effective in achieving reductions in BMI and blood pressure in screen-detected type 2 diabetes patients up until nine months follow-up. However, its long-term effectiveness in people already known with diabetes is lacking. In addition, its (cost-) effectiveness might increase if people who are likely not to be benefit from the program are excluded in a valid way. Therefore it was aimed to investigate the long-term effects of the educational program BGI on cardiovascular risk, quality of life and diabetes self-management behaviour in a pre-selected group of patients known with type 2 diabetes up to 5 years.

**Methods:**

Randomised controlled trial with 2.5 year follow-up. Adults (≤75 years) with a type 2 diabetes duration between 3 months and 5 years will be included. With the use of a self-management screening tool (SeMaS) their potential barriers of self-management due to depression and/or anxiety will be determined. Based on the results of the SeMaS selection patients will be randomised (1:1) to the BGI-group (n = 53) or the control-group (n = 53). In addition to receiving usual care, patients in the BGI-group will follow the 12-week theory-based self-management program and a booster session a few months thereafter. The control-group will receive care as usual. The primary outcome is change in Body Mass Index after 2.5 years follow-up. Secondary outcomes are HbA1c, lipid profile and systolic blood pressure, (diabetes) quality of life, level of physical activity, dietary intake and medication adherence and proactive coping. Cost-effectiveness will be based on total use of health care resources during the entire study period. Difference between groups in change over time will be analysed according to intention-to-treat analysis.

**Conclusions:**

By differentiating between patients who will and those who are likely not to benefit from the educational program, a more (cost-) effective self-management program might be designed, also on the long-run.

*Trial registration* NTR 5330

## Background

Diabetes self-management forms a major part of diabetes treatment and involves several complex behaviours, such as adhering to a treatment regimen, monitoring symptoms, maintaining a healthy lifestyle and managing the impact of the disease on one’s life. People with type 2 diabetes mellitus (T2DM) are expected to take more and more responsibility in this, but for many of them self-management is difficult to incorporate in daily life and not all patients will possess the necessary skills for this. The motivation to initiate changes in behaviour is often present, but patients do not know what needs to change or maintain the achieved behavioural lifestyle when barriers are encountered. We developed the Beyond Good Intentions (BGI) program to enhance the ability of patients to act upon their intentions. It is based on the theories of self-regulation and proactive coping [1], assuming that people should control and direct their actions in order to meet their goals. Pro-active coping refers to efforts undertaken in advance of a potentially stressful event to prevent or modify its form before it occurs [1]. BGI has proven to be effective in patients with screen-detected T2DM up until 9 months follow-up [2]. Based on a computer-based simulation model to project long-term health benefits and cost-effectiveness, BGI was among the four diabetes self-management programs worldwide, with a minimum follow-up of 12 months, with the best cost-effectiveness ratio [3]. However, real, not modelled, long-term data on (cost-) effectiveness of BGI are lacking and also its effectiveness in people who are known with T2DM and not screen-detected, is unclear.

Group based educational programs for diabetes self-management can improve blood glucose, blood pressure, body mass index (BMI) and the requirement of blood glucose lowering drugs; however, the long-term results were varying [4]. In Italy, non-insulin-treated T2DM patients known with diabetes for at least 1 year were randomised to either group or individual care in a hospital-based setting. After 4 years clinical, cognitive, and psychological outcomes were better in the group based treatment [5]. In the DESMOND trial, greater improvements in weight loss and smoking cessation were found in the intervention group at 1-year-follow-up, but at 3-year-follow-up this effect was no longer apparent [6, 7]. In general, completers of a diabetes self-management intervention study are significantly more highly educated than dropouts [8]. This indicates that interventions to improve self-management should be tailored to different categories of patients. The ‘one size fits all’ principle in diabetes education research is outdated. To estimate a priori the chance of successful self-management of a patient, the self-management screening tool (SeMaS) can be used [9]. With SeMaS possible barriers for self-management due to depression and/or anxiety can be detected. Both depression and anxiety can interfere with the effectiveness of a self-management program at that moment for a particular person and should be dealt with before following the program. Besides, individuals with already high self-management capabilities are likely to have no additional benefit from an educational course [10–12].

We hypothesise that by differentiating between patients who may and those who may not benefit from a self-management program, a more (cost-) effective self-management education program can be designed which is also effective on the long-run. Therefore, the aim of the current study is to investigate the cost-effectiveness and long-term effects of the educational program BGI on cardiovascular risk, quality of life and diabetes self-management behaviour in a preselected group of known T2DM patients.

## Methods

### Setting

In Dutch primary care, most patients (80–85%) are treated within disease management programs, contracted by so called care groups. These care groups are responsible for the organisation, coordination and delivery of diabetes care in primary care [13, 14]. Three care groups with 43 general practices (both group and single handed practices, with 89 general practitioners) in the southern part of the Netherlands participate in the current study.

### Study design and selection criteria

The study is designed as a parallel randomised controlled trial with 2.5 years follow-up and will follow the CONSORT criteria for experimental designs [15]. Along with the BGI self-management education program (obviously only for the intervention group) all participants will receive diabetes care according to the guidelines of the Dutch College of General practitioners [16].

#### Inclusion criteria

Adults, aged ≤75 years.Diagnosed with T2DM between 3 months–5 years ago.

#### Exclusion criteria

High self-management capability on all SeMaS domains (see below).High scores on the SeMaS domains ‘Anxiety’ or ‘Depression’ (see below).Insufficient cognitive functioning.Insufficient understanding of the Dutch language to follow instructions and to complete questionnaires.

### Ethical approval

The study was approved by the Medical Ethical committee of the University Medical Centre Utrecht and registered at the Dutch Trial Register (Netherlands Trial Register NTR5330).

### Recruitment

The electronic medical records from the people with T2DM from the participating general practitioners are scrutinised to find eligible T2DM patients. All patients who meet the inclusion criteria will be informed about the possibility to follow a group-based diabetes self-management education program with pre-selection (see further), emphasising that they will be only offered an educational program they are likely to benefit from. People can indicate on a response card whether or not they want to receive oral information about the study. If yes, a research team member will give the patient a telephone call to discuss the study. If the patient is informed and understands the information, informed consent will be completed. Once the patient has given informed consent the pre-selection will take place.

### Pre-selection

The pre-selection procedure to assess a patient’s capabilities of self-management will be performed with the use of the SeMaS, a self-management screening tool which is validated in T2DM patients and sent to the patients home [9]. The SeMaS is a 27 item questionnaire covering self-management abilities of five psychosocial domains [locus-of-control (3 items), self-efficacy (2 items), social support (1 items), coping (9 items), anxiety (4 items) and depression (3 items)], three skills items (computer, group and self-care) and two other items including perceived burden of disease [9]. All separate items range from 0 to 3 on a 4-point Likert scale (locus-of-control, self-efficacy, coping, skills items) or from 0 to 2 on a 3-point Likert scale (social support, anxiety, depression). For all items higher scores represent higher capability, except for those in the anxiety and depression domain where higher score represent more barriers. The perceived burden of disease is scored on a visual analogue scale from 0 to 10. Patients with high scores on the domains anxiety (score >4 from total 8) and/or depression (score >3 of total 6) will be excluded during the pre-selection. Those patients first need to deal with their mood disturbance before they are able to improve their self-management skills. Patients without barriers for self-management, so with maximal self-management capacity (highest possible scores for the locus-of-control, self-efficacy, social support, coping and for anxiety ≤4 and for depression ≤3) were also excluded, since they would not benefit from the educational course. The general practitioner (GP) will be informed about the SeMaS scores of all participants.

### Randomisation

Patients who are eligible after the pre-selection will be randomised (1:1) based on computer-generated random numbers, with sealed, opaque, sequentially numbered allocation envelopes. All patients entering the trial receive a random number from the coordinating research centre (Julius Center). Each number corresponds to either ‘BGI course’ (BGI-group) or ‘no BGI course’ (control-group). As patients will attend a course in the intervention group, it is not possible to blind participants for the treatment allocation. Patients from the same practices and general practitioners will attend a different course, so no large cluster-effect is expected.

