#### Group sessions

The group sessions are held in groups of six to ten participants and take place every two to three weeks in a location nearby the patients’ homes. The first three sessions will cover topics that are relevant for all patients: physical activity, healthy diet and medication adherence (what do guidelines tell, why it is important to follow these guidelines and how to do it, what are known barriers in this respect, what might facilitate compliance, followed by individual goals to improve). In the fourth session patients will be able to work on a personally relevant goal.

Every group session starts with the introduction of the topic, patients are asked to share their opinions, emotions and experiences regarding the topic. Subsequently, patients write their own individual action plan, according to the proactive coping five-step plan:Step 1: Formulate a concrete and attainable goal.Step 2: What are necessary conditions and possible barriers?Step 3: What may be alternative strategies for crossing these possible barriers?Step 4: Formulate the final plan: what, how, where, and when?Step 5: Indicate how the progress will be evaluated and when you are satisfied, the plan is discussed with the group to improve the final plan.

During the weeks in between the groups sessions patients will practice with their individual action plane, which will be evaluated during the next meeting.

In case of diabetes-related questions, patients are encouraged to collect additional information by themselves, e.g. on the Internet or by referring them to another professional like a physiotherapist or dietician. This way, patients are encouraged to take responsibility for their disease.

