### Nurse training

The BGI course will be given by trained practice nurses (n = 3). They receive two 3-h training sessions from the psychologist who is familiar with the BGI training (Train-the-trainer principle). During the training they will work with the five-step proactive coping plan and will be taught on the principles of the self-regulation and pro-active coping theory. The practice nurse should have the role of facilitator and coach, stimulating participants to support each other and become self-confident in seeking information.

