### Statistical analyses

The efficacy analysis will be performed by intention-to-treat analysis, including all patients from whom a follow-up assessment is available. If necessary a multiple imputation technique will be used for missing data. The primary outcome will be analysed by using Generalized Estimated Equations (GEE) for repeated measures, with baseline BMI as covariate and time, intervention and the interaction of time and intervention as fixed variables. The secondary outcomes will be analysed with ANCOVA on the change from baseline to follow-up. In addition differences in characteristics (e.g. age, sex, education level) of participants and non-participants will be evaluated.

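### The reason given for expecting no large cluster effect covers practices and GPs only; correlation arising within the BGI course groups is left out of both the sample size and the stated models

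*Protocol article*

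**What the plan says.** All places are in the protocol article.

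- **Randomisation.** Allocation is by individual patient: "Patients who are eligible after the pre-selection will be randomised (1:1) based on computer-generated random numbers". On clustering the section says: "Patients from the same practices and general practitioners will attend a different course, so no large cluster-effect is expected".
- **Group sessions.** "The group sessions are held in groups of six to ten participants", held "in a location nearby the patients’ homes". Participants exchange experiences, and each action plan goes to the group for improvement. There are four such sessions plus a booster.
- **Nurse training.** "The BGI course will be given by trained practice nurses", three in number, whose role includes getting participants to support one another.
- **Control group.** Usual care only, with no group component.
- **Sample size.** 44 per group, from six BMI measurements with an AR(1) structure. The only correlation entered is within patient.
- **Statistical analyses.** "The primary outcome will be analysed by using Generalized Estimated Equations (GEE) for repeated measures", with baseline BMI, time, intervention and their interaction. Secondary outcomes use ANCOVA on change from baseline. No course or nurse level is named.

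**The concern.** The reason and the conclusion in the Randomisation section concern different clusters. Spreading a practice's patients over several courses stops practice and course from coinciding. It does nothing about patients becoming alike because they sat in the same course. Practice was never the likely main source: the Setting section gives 43 practices, so 53 BGI patients are about 53/43 = 1.2 per practice.

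The course is the more plausible source, since group discussion and mutual support are part of how BGI is meant to work. It exists in one arm only, so the design is partially nested. A GEE clustered on patient, robust variance included, still treats patients as independent of each other, and so does ANCOVA. If outcomes within a course are positively correlated, the standard error of the BGI mean is understated, confidence intervals are too narrow, and the planned sample size is somewhat optimistic.

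**Working it through.** **Inputs from the protocol article.** Difference 0.77, SD 1.7, six measurements, AR(1) correlation 0.70, alpha 0.05 (taken as two-sided), power 80%, 44 evaluable per group, 20% dropout (Sample size); 53 per arm (Abstract); course groups of 6 to 10 (Group sessions); three nurses (Nurse training).

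**Assumed.** ICC within course group of 0.01, 0.05 or 0.10 on each patient's average follow-up BMI. The document gives none.

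**1. Reproducing the plan's figure.** Variance factor for the mean of six AR(1) measurements: [6 + 2(5×0.7 + 4×0.49 + 3×0.343 + 2×0.2401 + 0.16807)]/36 = 20.27/36 = 0.563. SD of the mean = 1.7 × √0.563 = 1.276. n per group = 2 × [1.276 × (1.960 + 0.842)/0.77]² = 43.09, rounded up to 44. The stated figure is reproduced with independent patients, so it contains no allowance for clustering. With 44 per group the standard error is 1.276 × √(2/44) = 0.272 and power is 80.8%.

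**2. Number of course groups.** 53/10 = 5.3 and 53/6 = 8.8. Five groups hold at most 50 patients and nine need at least 54, so 6 to 8 groups are possible within the stated sizes.

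**3. Evaluable patients per group.** A mid-sized group of 8 with 20% dropout leaves 8 × 0.8 = 6.4.

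**4. Effect of clustering in one arm.**
- Design effect in the BGI arm: DE = 1 + (m − 1) × ICC, with m = 6.4.
- True SE divided by patient-level SE: k = √[(1 + DE)/2].
- Type I error of the planned test: 2 × [1 − Φ(1.96/k)].
- Power of a test using the correct SE: Φ(0.77/(0.272k) − 1.96).
- Rejection probability of the planned, unadjusted test at a difference of 0.77: Φ[(0.77/0.272 − 1.96)/k].

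| ICC (assumed) | DE | k | Type I error, planned test | Power, adjusted test | Rejection at 0.77, planned test |
|---|---|---|---|---|---|
| 0.01 | 1.054 | 1.013 | 5.3% | 79.8% | 80.5% |
| 0.05 | 1.27 | 1.065 | 6.6% | 75.7% | 79.3% |
| 0.10 | 1.54 | 1.127 | 8.2% | 71.0% | 78.0% |

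The last two columns describe different tests. The planned test loses little rejection probability because its standard error is too small. The loss shows once the error rate is controlled.

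**5. Sensitivity to group size.** With no loss from groups of 8, k is 1.017, 1.084 and 1.162, type I error is 5.4%, 7.1% and 9.2%, and adjusted power is 79%, 74% and 68%.

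These are normal approximations with the ICC treated as known. Degrees of freedom suited to 6 to 8 groups would lower adjusted power further.

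**The case against.** **The ICC is unknown.** This stands. The sign and the size both rest on an assumed positive ICC. At 0.01 the effect is trivial and fits the protocol's wording, which says no large effect is expected rather than none. A reader might infer that the documents show the standard errors to be too small, or the expectation to be false. They show neither, only that the reason offered does not support the expectation.

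**If BGI affects nobody, the course creates no correlation.** This also stands. Patients are individually randomised, so under a strict null of no effect on anyone this route does not inflate the type I error. The figures above apply when course effects differ between groups but average to zero. For interval estimation this limit matters less: if BGI works better in some courses than in others, the interval for its average effect is too narrow whether or not that average is zero.

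**The planned test barely loses power.** Correct for the unadjusted test, as the last column of the table shows. A reader might set inflated error and lost power side by side as properties of one analysis; they are not.

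**An analysis plan may add a course term.** Possible, and its absence from an article is not in itself the fault. The article, however, takes a position on clustering, gives a reason that concerns another kind of cluster, and lists the model terms without a course level. An analyst who follows it has grounds to leave the term out.

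**Conclusion.** The stated rationale does not cover the clustering that the design is most likely to produce, and neither the sample size nor the described models make up for that. How much it matters depends on an ICC the document does not give: negligible at 0.01, and material at 0.05 to 0.10, where the true standard error is about 7% to 13% larger than the patient-level one. This assumes a positive ICC, about 6.4 evaluable patients per course group, and no grouping among controls. There is little slack to absorb it: 106 × 0.8 = 84.8 completers give 79.4% power even with independent patients. The plan should be changed here, but this is no ground for calling the trial invalid.

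**What to change.** 1. In the Randomisation section, limit the sentence to clustering by practice and GP, and state that course-group clustering in the BGI arm is handled in the analysis.
2. Record course group and nurse for every BGI patient. Without this the question cannot be examined afterwards.
3. Prespecify a partially nested mixed model: a random course-group effect in the BGI arm only, repeated measures within patient, and Satterthwaite or Kenward-Roger degrees of freedom. Make it the primary analysis or at least a sensitivity analysis beside the GEE. Give the secondary ANCOVAs a matching course-group term.
4. Report the estimated ICC with its uncertainty, and restate power over an ICC range such as 0.01 to 0.10.
5. Do not fit a nurse variance: three nurses are too few to estimate it. Describe results by nurse instead.

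**Cost.** Two recorded variables and a respecified model. As the primary analysis, the mixed model replaces the GEE, which is more than adding one term. Confidence intervals will generally be wider, and the course-group variance will rest on only 6 to 8 groups and so be imprecise. Treatment, recruitment and visits do not change.

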### Intervention: beyond good intentions (BGI)

This study elaborates on the existing self-management program BGI [2, 17, 18]. It lasts 12 weeks and consists of one initiating 30-min individual session and four 2.5-h group sessions. In addition, one booster-session is given a few months after the last group session. The course structure is as follows:

#### Individual session

The patient’s knowledge, attitudes and ambivalence with regard to diabetes management will be discussed. For this purpose the ‘Diabetes Profile’ was specifically designed to help patients gaining insight in the risk factors associated with their diabetes. With a colour scheme, from green to red, their risk for long-term complications is presented. Patients are encouraged to set goals to work on. The trained practice nurse (see further) discusses glycaemic control, BMI, blood pressure and lipids profile with the patient. Patients are asked to formulate a first goal before the first group session and will receive the educational material that will be discussed during the group sessions.

#### Group sessions

The group sessions are held in groups of six to ten participants and take place every two to three weeks in a location nearby the patients’ homes. The first three sessions will cover topics that are relevant for all patients: physical activity, healthy diet and medication adherence (what do guidelines tell, why it is important to follow these guidelines and how to do it, what are known barriers in this respect, what might facilitate compliance, followed by individual goals to improve). In the fourth session patients will be able to work on a personally relevant goal.

Every group session starts with the introduction of the topic, patients are asked to share their opinions, emotions and experiences regarding the topic. Subsequently, patients write their own individual action plan, according to the proactive coping five-step plan:Step 1: Formulate a concrete and attainable goal.Step 2: What are necessary conditions and possible barriers?Step 3: What may be alternative strategies for crossing these possible barriers?Step 4: Formulate the final plan: what, how, where, and when?Step 5: Indicate how the progress will be evaluated and when you are satisfied, the plan is discussed with the group to improve the final plan.

During the weeks in between the groups sessions patients will practice with their individual action plane, which will be evaluated during the next meeting.

In case of diabetes-related questions, patients are encouraged to collect additional information by themselves, e.g. on the Internet or by referring them to another professional like a physiotherapist or dietician. This way, patients are encouraged to take responsibility for their disease.

